#### Secondary outcomes

2.4.2

Part I: Clinical outcomes

1. Duration of ICU stay.

2. Duration of mechanical ventilation.

3. Duration of hospital stay.

4. 28-day mortality.

5. ICU-free to 28 days.

6. Hospital-free days to 28 days.

7. Ventilation-free days to 28 days.

8. Incidence of new-onset organ failure within 7 days after enrollment.

9. New receipt of organ support within the first 7 days.

10. Number of organ support–free days within the first 7 days.

11. Daily Sequential Organ Failure Assessment (SOFA) scores recorded over the first 7 days.

Part II: Nutritional outcomes

1. Time to initiation of EN.

2. Average daily energy intake within the first 7 days.

3. Average daily protein intake within the first 7 days.

4. Daily Bristol stool score within the first 7 days.

5. Daily Feeding Intolerance Score (FIS) (20) within the first 7 days (Supplementary Table 1).

6. Daily Gastrointestinal Dysfunction Score (GIDS) (21) within the first 7 days (Supplementary Table 2).

7. Proportion of patients who transition to postpyloric feeding within the first 7 days.

8. Proportion of receiving PN within the first 7 days.

9. Caloric adequacy on Days 3, 5, and 7, defined as achieving at least 80% of the estimated energy target.

10. Protein adequacy on Days 3, 5, and 7, defined as achieving at least 70% of a target of 1.3 g/kg/day.

Part III: Biochemical outcomes

Daily serum albumin, prealbumin, C-reactive protein (CRP), and blood urea nitrogen (BUN) during the first 7 days after enrollment.

Outcome definitions are as follows. *New-onset organ failure* is defined as failure arising in an organ system that was functionally intact at randomization, corresponding to an increase of ≥2 points in the SOFA sub-score for the respiratory, circulatory, or renal system relative to baseline. SOFA scores are assessed daily for the first 7 days following randomization. *New receipt of organ support therapy* refers to the initiation of mechanical ventilation, renal replacement therapy, or vasoactive agents that were not being used at enrollment. *Daily energy and protein intake* will be calculated based on EN, PN, and quantifiable oral nutritional supplements, with non-quantifiable oral intake excluded.

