### Data collection and management

2.5

Data will be collected and stored using a secure, web-based electronic data capture system (Unimed Science Inc., Wuxi, China). At each participating center, the principal investigator will be responsible for oversight of patient enrollment and data entry. Data entry will be performed exclusively by the principal investigator or by up to two designated research staff members authorized by the principal investigator.

Standardized training in data entry and database use will be provided by the database vendor in collaboration with the CCCNTG coordinating center. All data required to characterize baseline patient characteristics (Table 1), study and control interventions, potential confounding co-interventions, and study outcomes will be systematically and prospectively collected in accordance with the study protocol. Table 2 shows the schedule of enrolment, interventions, and main data collected.

**TABLE 1 T1:** Baseline characteristics of patients by treatment group.

Characteristics	Pectin group (*n* = xx)	Control group (*n* = xx)
Age, years		
Male gender, no. (%)		
BMI, kg/m^2^		
Admission diagnosis, no. (%)		
Respiratory		
Cardiovascular		
Gastrointestinal		
Neurological		
Sepsis		
Trauma		
Others		
ICU source of admission, no. (%)		
Emergency		
Medical		
Surgical		
Others		
Comorbidities, no. (%)		
Hypertension		
Coronary disease		
Diabetes		
Chronic respiratory diseases		
Stroke		
Gastrointestinal disease		
Malignant tumor		
Others		
Interval from ICU admission to randomization, days		
APACHE II score		
SOFA score		
mNUTRIC score		
Presence of organ failure at baseline, no. (%)		
Respiratory		
Renal		
Cardiovascular		
Organ support at baseline, no. (%)		
Renal replacement therapy		
Vasoactive drugs		
Serum albumin, g/L		
Serum creatinine, μmol/L		
BUN, mmol/L		
CRP, mg/L		
PPIs use before randomization, no. (%)		

BMI, body mass index; ICU, intensive care unit; APACHE II, Acute Physiology and Chronic Health Evaluation II; SOFA, Sequential Organ Failure Assessment; mNUTRIC, modified Nutrition Risk in the Critically Ill; BUN, blood urea nitrogen; CRP, C-reactive protein; PPI, proton pump inhibitor.

**TABLE 2 T2:** Schedule of enrolment, intervention, and data collection.

	Study period									
Time point	Screening	Randomiza-tion	After randomization/day							End
		0	1	2	3	4	5	6	7	28
Enrollment										
Eligibility screen	×	–	–	–	–	–	–	–	–	–
Informed consent	×	–	–	–	–	–	–	–	–	–
Allocation	–	×	–	–	–	–	–	–	–	–

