Intervention										
Intervention group	–	×	×	×	×	×	×	×	×	–
Control group	–	×	×	×	×	×	×	×	×	–
Assessments										
Baseline characteristics	×	×	–	–	–	–	–	–	–	–
Laboratory parameters	–	–	×	×	×	×	×	×	×	–
APACHE II score	–	–	×	×	×	×	×	×	×	–
SOFA score	–	–	×	×	×	×	×	×	×	–
mNUTRIC score	–	–	×	×	×	×	×	×	×	–
Feeding Intolerance Score (FIS)	–	–	×	×	×	×	×	×	×	–
Gastrointestinal Dysfunction Score (GIDS)	–	–	×	×	×	×	×	×	×	–
Bristol stool score	–	–	×	×	×	×	×	×	×	–
Daily energy intake	–	–	×	×	×	×	×	×	×	–
Daily protein intake	–	–	×	×	×	×	×	×	×	–
Caloric adequacy	–	–	–	–	×	–	×	–	×	–
Protein adequacy	–	–	–	–	×	–	×	–	×	–
New-onset organ failure	–	–	×	×	×	×	×	×	×	–
Receipt of organ support	–	–	×	×	×	×	×	×	×	–
Clinical outcomes	–	–	–	–	–	–	–	–	–	×
Adverse events	–	–	×	×	×	×	×	×	×	×

APACHE II, Acute Physiology and Chronic Health Evaluation II; SOFA, Sequential Organ Failure Assessment; mNUTRIC, modified Nutrition Risk in the Critically Ill.

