Statistical methods: Normality of continuous variables will be assessed using the Shapiro-Wilk test. Normally distributed continuous variables will be summarized as mean ± standard deviation and compared using Student’s *t*-test; non-normally distributed variables will be summarized as median (interquartile range, IQR) and compared using the Mann-Whitney U test. Categorical variables will be summarized as counts and percentages and compared using Pearson’s chi-square test. Effect estimates with 95% confidence intervals (CIs) will be reported throughout. No adjustment for multiple comparisons will be applied; all secondary outcome analyses are considered exploratory and hypothesis-generating. For secondary outcomes, complete-case analysis will be used, with missing data rates reported for each outcome. A two-sided *P*-value < 0.05 will be considered statistically significant.

Subgroup analyses: Pre-specified subgroup analyses will be conducted according to the following baseline characteristics: age (>60 vs. ≤59 years), BMI (>25 vs. ≤25 kg/m^2^), SOFA score (≥9 vs. <9), and ICU admission type (emergency, surgical, medical, or other).

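### The daily albumin, CRP, BUN and SOFA comparisons leave out baseline values that Table 1 already collects, which costs precision, and no pre-treatment prealbumin value is listed

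*Protocol article*

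**What the plan says.** **Outcomes.** Part III of section 2.4.2 lists "Daily serum albumin, prealbumin, C-reactive protein (CRP), and blood urea nitrogen (BUN) during the first 7 days after enrollment". Part I of the same section adds "Daily Sequential Organ Failure Assessment (SOFA) scores recorded over the first 7 days". Neither is defined as a change from baseline or refers to a baseline value.

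**Analysis.** Section 2.7 gives one general rule for continuous variables, chosen by a Shapiro-Wilk test. Normally distributed variables are "compared using Student’s *t*-test; non-normally distributed variables will be summarized as median (interquartile range, IQR) and compared using the Mann-Whitney U test". The rule names no covariate, change score or repeated-measures model. The section also labels all secondary outcomes exploratory and analyses them on complete cases.

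**Baseline data.** Section 2.5 says that the Table 1 items are collected prospectively. Table 1 lists serum albumin, BUN, CRP and the SOFA score. It does not list prealbumin.

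**Schedule.** In Table 2 the row "Laboratory parameters" has a dash at screening and at randomization and crosses on Days 1 to 7. The intervention row is marked from randomization (Day 0). A separate row for baseline characteristics is marked at screening and at randomization.

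**The concern.** Patients enter within 24 hours of ICU admission, and these markers and the SOFA score can be expected to differ widely between patients at that point. Where values over the following week track the entry value, an unadjusted comparison leaves that entry variation in the error term, although the trial holds the data to remove it. The result is wider intervals than necessary for the outcomes meant to generate hypotheses about nutritional and inflammatory response.

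Prealbumin is in a weaker position than the other three markers. With no pre-treatment value listed, the listed data allow neither adjustment nor a check on how the arms compared at entry.

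**Working it through.** **The plan's own figure.** The only sample size in the article is for the primary outcome. The difference is 0.20 × 62.9 = 12.58 percentage points, with SD 31.1, 80% power and two-sided alpha 0.05:

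n per arm = 2 × (1.960 + 0.842)² × 31.1² / 12.58² ≈ 96.

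Then 96 × 1.10 = 105.6, so 106 per arm and 212 in total. Both figures reproduce, and this point does not affect them.

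**Inputs for the check**
- n = 106 per arm (section 2.6). This is an upper limit for any one day, because secondary outcomes are complete-case and patients may die or leave the ICU.
- r, the correlation of an outcome with its own baseline: not in the documents. Assumed range 0.3 to 0.7.
- All results are in units of the outcome's SD, for a comparison of means.

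**Formulas**
- Unadjusted detectable difference at 80% power: (1.960 + 0.842) × √(2/106) = 2.802 × 0.137 = 0.385 SD.
- Adjusting for baseline multiplies the residual variance by 1 − r², and the interval width and detectable difference by √(1 − r²).
- Unadjusted n per arm needed to match 106 adjusted: 106 / (1 − r²).

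| r (assumed) | 1 − r² | Width factor | Interval narrower by | Detectable difference (SD) | Unadjusted n per arm to match |
|---|---|---|---|---|---|
| 0.3 | 0.91 | 0.954 | about 5% | 0.367 | 116 |
| 0.5 | 0.75 | 0.866 | about 13% | 0.333 | 141 |
| 0.7 | 0.51 | 0.714 | about 29% | 0.275 | 208 |

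**The same cost seen conditionally.** The standard error of a baseline difference is √(2/106) = 0.137 SD, so a difference of 1.96 × 0.137 = 0.27 SD is at the edge of ordinary chance. It moves the unadjusted contrast by r × 0.27, that is 0.08, 0.135 or 0.19 SD for r = 0.3, 0.5 or 0.7. Averaged over all possible imbalances the shift is zero, and the unadjusted interval already allows for it. It is not an error to be added to the loss in the table.

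**Prealbumin.** Its absence from Table 1 is the main evidence. The Table 2 laboratory row adds little alone, because it has the same Day 0 dash for albumin, CRP and BUN, which Table 1 does list at baseline.

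**The case against.** The strongest reply is that this is a preference about efficiency and not an error. Randomization makes the unadjusted contrast valid, the outcomes are exploratory, and an analysis plan that is not shown could add a covariate or longitudinal model. The section 2.7 rule is generic, names no biomarker and does not say how seven daily values are combined. Much of this stands, and it is why the point is minor. It does not remove the point. The article does not leave the method open: it states unadjusted tests for continuous variables, and as written those tests pass over baseline data already being collected.

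The size of the gain is also open to challenge. The correlation is assumed and may differ by marker and by day; at 0.3 the gain is only about 5%. That stands too.

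Three stronger readings are tempting, and the documents do not support them:
- *A reader might infer that the biomarker comparisons are biased or have an inflated false-positive rate.* They are unbiased on average, with 5% type I error overall.
- *A reader might infer that the Table 1 baselines are never used.* For SOFA this is wrong: new-onset organ failure is defined by a rise in SOFA sub-scores from baseline, and baseline SOFA defines a subgroup.
- *A reader might infer that prealbumin is not sampled before treatment at all.* The documents show only that no such value is listed. Table 1 is a reporting shell, not an assay list, and the Table 2 laboratory row cannot prove that no baseline blood was taken. The outcome is also defined as daily values, so it does not depend on a change score.

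**Conclusion.** The point holds as a low-severity improvement. The stated unadjusted tests make the daily albumin, CRP, BUN and SOFA comparisons less precise than the collected data allow. Over assumed correlations of 0.3 to 0.7 the gain from adjustment runs from slight to substantial, as tabulated. The proportional narrowing does not depend on the number of patients, but the detectable differences assume all 106 per arm and will be larger on days with fewer. The figures are for comparisons of means and serve only as a guide where the rank test would have been used.

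For prealbumin the conclusion is narrower: no pre-treatment value is listed, and Tables 1 and 2 do not agree on when laboratory values are first taken. The primary outcome, the sample size and the validity of the trial are untouched.

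**What to change.** 1. In section 2.7, or in the analysis plan, state that daily albumin, CRP, BUN and SOFA are each compared between arms with the baseline value of the same variable as a covariate. This can be ANCOVA by day, or one repeated-measures model with baseline and day. Log-transform CRP. Settle the choice before unblinding.
2. Reconcile Tables 1 and 2 so that they show which laboratory values are taken before the first pectin bolus, and say whether prealbumin is among them.
3. Use a pre-bolus prealbumin value as covariate where one is available. Otherwise report prealbumin as a post-treatment comparison only, and label it so.

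The first and third items change only analysis and reporting wording, and the second only the tables. None needs more patients or new data.

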## Introduction

1

Early initiation of enteral nutrition (EN) is critical for critically ill patients. Both ASPEN and ESPEN guidelines recommend starting EN with 48 h rather than delaying EN or initiating early parenteral nutrition (PN) (1, 2). Gastric delivery remains the standard initial route. However, EN frequently fails due to feeding intolerance, which affects approximately 20%–30% of critically ill patients and presents with elevated gastric residuals, nausea, vomiting, abdominal distension, or diarrhea (3, 4). Furthermore, this intolerance is associated with serious risks such as aspiration, inhalation pneumonia, and potentially fatal outcomes (5).

Current strategies for managing feeding intolerance are limited. Initial measures include prokinetic agents (e.g., erythromycin, metoclopramide) and formula adjustments, followed by post-pyloric feeding if needed (6, 7). If intolerance persists despite these interventions, PN is initiated. However, this stepwise approach is not always effective and can be time-consuming, potentially depriving patients of adequate EN and its associated benefits (7, 8). Feeding intolerance may be directly related to EN itself (9). For instance, the high osmolarity of EN formulations can contribute to diarrhea (10), while the low viscosity and high infusion rate may increase the risk of gastroesophageal reflux and subsequent aspiration (11).

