### Study design, setting, and population

2.1

PROMOTE is a multicenter, open-label, randomized, parallel-controlled trial conducted by the Chinese Critical Care Nutrition Trials Group (CCCNTG). The trial will enroll 212 critically ill adult patients from ten intensive care units (ICUs) across China. Trial oversight will be provided by a Trial Management Committee (TMC), comprising the principal investigators from each participating center and key members of CCCNTG, which will be responsible for the overall conduct and coordination of the study. Recruitment started in February 2024 with competition for enrollment expected in 2026. The trial protocol was developed according to the Standard Protocol Items: Recommendations for Interventional Trials (SPIRIT) statement (18).

Patients aged ≥ 18 years and within 24 h of their index ICU admission will be screened for eligibility. Those requiring invasive mechanical ventilation and, therefore, unable to take oral nutrition, necessitating artificial nutritional support, will be eligible for inclusion. The complete inclusion and exclusion criteria are listed below:

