#### Inclusion criteria

2.1.1

1. Aged ≥ 18 years old;

2. Admitted to ICU < 24 h;

3. Receive invasive mechanical ventilation < 72 h, and the expected duration of continued treatment > 48 h;

4. Do not expect to feed orally for more than 3 days and plan to receive gastric feeding;

5. No operation plan within a week;

6. Informed consent form obtained from the patient or next of kin.

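### Every patient is ventilated at entry, so the ventilation part of new receipt of organ support cannot occur and reintubation is not counted

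*Protocol article*

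**What the plan says.** **Entry.** Section 2.1 of the protocol article makes ventilation the basis of eligibility: "Those requiring invasive mechanical ventilation and, therefore, unable to take oral nutrition, necessitating artificial nutritional support, will be eligible for inclusion". Inclusion criterion 3 in section 2.1.1 repeats it with time limits: "Receive invasive mechanical ventilation < 72 h, and the expected duration of continued treatment > 48 h".

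**New receipt of organ support** (section 2.4.2, clinical outcome 9, first 7 days). The definition "refers to the initiation of mechanical ventilation, renal replacement therapy, or vasoactive agents that were not being used at enrollment".

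**New-onset organ failure** (section 2.4.2, clinical outcome 8, within 7 days). This is defined as "failure arising in an organ system that was functionally intact at randomization", and is said to correspond to "an increase of ≥2 points in the SOFA sub-score for the respiratory, circulatory, or renal system relative to baseline".

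**Baseline table.** Under "Organ support at baseline, no", Table 1 lists renal replacement therapy and vasoactive drugs only. Under "Presence of organ failure at baseline, no", it lists respiratory, renal and cardiovascular failure, each to be shown as a count and percentage.

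**Data schedule.** Table 2 schedules SOFA, new-onset organ failure and receipt of organ support on each of Days 1 to 7.

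**The concern.** A component of a composite outcome should be able to occur in at least some enrolled patients. Here the entry criterion and the outcome definition appear to exclude each other: ventilation is required for entry, yet counts as new only if absent at entry.

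The respiratory system matters to this trial's rationale. The Introduction ties feeding intolerance to aspiration ("this intolerance is associated with serious risks such as aspiration, inhalation pneumonia, and potentially fatal outcomes"), and section 2.3.1 expects pectin to reduce retrograde flow and reflux. Return to the ventilator after extubation is one event through which benefit or harm of that kind could appear. If the outcome is reported as covering ventilation, renal replacement and vasoactive support, a finding of no difference could be taken to include ventilation when no ventilation event could have been recorded.

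New-onset organ failure raises a smaller question. It is unclear which ventilated patients count as having an intact respiratory system, and so which of them can have a respiratory event.

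**Working it through.** The plan states no figure on this point, so the check is mainly one of logic.

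**1. Ventilation component of new receipt of organ support**
- Condition A (sections 2.1 and 2.1.1): the patient is on invasive mechanical ventilation at entry. It holds for all eligible patients, and the planned number is 212 (section 2.1).
- Condition B (section 2.4.2): the support was not in use at enrollment.
- For ventilation, A and B cannot both hold. Number at risk = 212 × 0 = 0.
- Table 1 fits this: ventilation is absent from its list of baseline supports, as expected if everyone has it.

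**2. Reintubation**
- Take a patient extubated on Day 3 and reintubated on Day 4. Ventilation is started again, but the definition tests status at enrollment, not status just before the event. Ventilation was in use at enrollment, so no event is scored.

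**3. What remains**
- Of three named supports, two can generate events: renal replacement therapy and vasoactive agents, each in patients not receiving it at enrollment.

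**4. Respiratory component of new-onset organ failure**
- The definition names the respiratory sub-score, so a patient with an intact respiratory system at randomization whose sub-score rises by 2 or more is an event. This component is not void.
- The definition gives no sub-score that counts as intact. For a ventilated patient going from 2 to 4, the rise is met but the intact condition is open to dispute.
- The share of patients with an intact respiratory system is not in the document. Over an assumed range of 5% to 40%, number at risk = 212 × share:

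| Assumed share intact | Calculation | At risk |
|---|---|---|
| 5% | 212 × 0.05 = 10.6 | about 11 |
| 10% | 212 × 0.10 = 21.2 | about 21 |
| 20% | 212 × 0.20 = 42.4 | about 42 |
| 30% | 212 × 0.30 = 63.6 | about 64 |
| 40% | 212 × 0.40 = 84.8 | about 85 |

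The range is an assumption and is wide. It shows a reduced at-risk set of unknown size.

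**The case against.** **The outcomes are exploratory, and the respiratory course is captured elsewhere.** Section 2.7 declares all secondary analyses exploratory. Section 2.4.2 also lists duration of ventilation, ventilation-free days and daily SOFA, and sections 2.8 and 2.9 monitor aspiration pneumonia. This stands as a limit on importance: nothing here touches the primary outcome or the sample size. It does not justify keeping a component that cannot occur. None of the listed outcomes identifies reintubation as an event. The aspiration pneumonia definition in section 2.9 is tied to the time of pectin administration, so as worded it does not give a comparison between arms.

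**Initiation could be read to include reintubation.** The qualifier refers to use at enrollment, so the text does not support that reading. If some of the ten sites adopted it and others did not, the outcome would be recorded inconsistently.

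**A stronger reading is tempting: that the respiratory part of new-onset organ failure is almost empty too, so that neither outcome can register respiratory deterioration.** The document does not support this, for three reasons:
- Nowhere does it equate being ventilated with having a respiratory system that is not intact.
- Table 1 plans to tabulate baseline respiratory failure as a count and percentage, and lists neurological and trauma admissions, so it treats respiratory failure as variable.
- The wording that links the two parts of the definition can be read as making the 2-point rise the working rule. On that reading the patient going from 2 to 4 counts.

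What survives for that outcome is only that the meaning of intact is not tied to a score.

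**Conclusion.** The point holds for new receipt of organ support. Its ventilation component is zero by construction in all 212 planned patients, reintubation is not counted, and one of the three named supports contributes nothing. This rests on two things: the entry criterion being met by those enrolled, and mechanical ventilation being treated as a single support, as the definition does.

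For new-onset organ failure the conclusion is weaker. The respiratory at-risk set is narrowed by an amount the document does not give, because the intact condition has no SOFA cut-off. That outcome can still register respiratory deterioration, and it should not be described as limited to circulatory and renal events.

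The correction is worth making because the fault lies in a stated definition and is cheap to repair. The consequence is confined to two exploratory secondary outcomes.

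**What to change.** In section 2.4.2, settle and document the following before any unblinded analysis:

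1. **Ventilation component.** Count re-initiation of invasive mechanical ventilation after liberation, within 7 days of randomization, with a stated minimum ventilator-free interval. Alternatively, remove ventilation and rename the outcome as new renal replacement therapy or vasoactive support.
2. **Reporting.** Show each component separately by arm. If re-initiation is used, keep all randomized patients in the denominator, because liberation happens after randomization and a comparison among extubated patients alone would not be a randomized one.
3. **New-onset organ failure (minor).** State one baseline sub-score rule for what counts as intact, and apply it to the respiratory, circulatory and renal systems alike. Dropping the intact condition for the respiratory system only would leave the composite with different definitions for different organs. Report the number at risk for each system.

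**Cost.** The change is to wording. Organ-support status and SOFA are already scheduled daily on Days 1 to 7, which should be enough to derive the events; if the required interval is shorter than a day, the recorded start and stop times need checking. One limit remains: a patient who is never liberated within 7 days cannot have a re-initiation event, so the result should be read beside duration of ventilation and ventilation-free days.
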